***Maternal health*****&*****well-being***								
General health status (EQ-5D) [52]	***x***	***x***		***x***	***x***	***x***	***x***	
Weight / BMI (Millennium Cohort Study) [50,51]	***x***						***x***	
Psychological distress (Kessler scale) [53]	***x***						***x***	
Depression (Whooley scale) [54]				***x***	***x***	***x***	***x***	
Postnatal depression (Edinburgh PDS) [55]				***x***				
Self-efficacy (Generalised Self-efficacy Scale) [56]	***x***			***x***	***x***	***x***	***x***	
Adaptive functioning [57,58]	***x***						***x***	
Intimate partner violence (Composite Abuse Scale) [59]							***x***	

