***Social support***								
Social support and networks (MOS Survey) [63,64]	***x***			***x***	***x***	***x***	***x***	
Family resources [65]	***x***			***x***	***x***	***x***	***x***	
Relationship quality (Golombok Rust Inventory of Marital State) [66]	***x***	***x***		***x***	***x***	***x***	***x***	

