### Statistical analysis

#### Main analysis – primary outcomes

The primary comparative analyses will be conducted on an intention-to-treat basis, with an emphasis placed on confidence intervals for differences between the randomised arms.

Descriptive statistics of demographic and outcome measures will be used to ascertain any marked imbalance between the arms at baseline. For birth weight and prenatal tobacco use at 34-36 weeks the primary comparative analyses will employ multivariable linear regression to investigate differences between the arms, adjusting for stratification/ minimisation variables. In the case of prenatal tobacco use the calibrated number of cigarettes per day reported at baseline will also be adjusted for. The result will be presented as the (adjusted) difference in mean number of cigarettes per day between the intervention and control arms. Parameter estimates will be shown alongside 95% confidence intervals (CIs) and p-values.

For the proportion of children with at least one emergency attendance and/or admission and proportion of women with known subsequent pregnancies, logistic regression will be used adjusting for stratification/minimisation variables. Comparisons will be presented as odds ratios, 95% CIs and p-values.

Multilevel modelling will be used to allow for clustering of effect within a site and Family Nurse. Where this analysis indicates little impact of clustering on effect then the results from the single level model will be presented. Sensitivity analyses will be conducted to investigate the potential impact of missing data, making different assumptions such as ‘best’ and ‘worst’ case scenarios as well as imputation models. Where variables exhibit marked imbalance at baseline, primary analyses will be repeated and adjustments will be made to check that this does not influence findings. The same analyses will be carried out for the secondary outcomes depending on the type of data.

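### Continuous secondary outcomes measured before randomisation are not committed to a main model that includes their own baseline value

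*Protocol article*

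**What the plan says.** Under Main analysis – primary outcomes, the protocol article sets out the covariates as follows.

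- Birth weight and prenatal tobacco use: "the primary comparative analyses will employ multivariable linear regression to investigate differences between the arms, adjusting for stratification/ minimisation variables".
- One addition: "In the case of prenatal tobacco use the calibrated number of cigarettes per day reported at baseline will also be adjusted for".
- Emergency attendance or admission, and second pregnancy: "logistic regression will be used adjusting for stratification/minimisation variables".
- Other baseline measures: descriptive statistics are used to look for marked imbalance between the arms, and then "Where variables exhibit marked imbalance at baseline, primary analyses will be repeated and adjustments will be made to check that this does not influence findings".
- Secondary outcomes: "The same analyses will be carried out for the secondary outcomes depending on the type of data".

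The Randomisation section gives the minimisation variables as gestation, smoking status and language, within site. None is a baseline score of a secondary outcome.

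Table 1 marks many secondary outcomes at baseline and again later, for example the rows beginning "Psychological distress (Kessler scale" and "Social support and networks (MOS Survey".

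**The concern.** The secondary-outcome rule selects the model by type of data, not by whether a baseline measurement exists. The text can be read in two ways. Either a continuous secondary outcome with a baseline follows the tobacco model, or it follows the default with stratification and minimisation variables only. The second reading is the likelier one, because the baseline value is introduced as a named addition for a single outcome. On neither reading is there a commitment, and the one written trigger for using other baseline measures depends on the observed data and an undefined threshold.

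What is at stake is the precision of the secondary results. The article places its emphasis on confidence intervals. For a scale score that correlates with its own baseline, leaving that value out makes the interval wider than the collected data require. A chance baseline difference then stays in the main estimate and is examined only if someone judges it marked.

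**Working it through.** **Step 1. Which outcomes are affected.** Tables 1 and 2 mark 16 non-primary outcomes at baseline and at one or more later points, all of them maternal.

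- Continuous or scale (7): EQ-5D, weight/BMI, Kessler distress, self-efficacy, MOS social support, family resources, relationship quality.
- Scale only if scored that way (2): adaptive functioning, CRAFFT.
- Binary or categorical by nature (7): NEET status, paid employment, type of employment, benefits, other financial support, homelessness, contraception.

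Among the four primary outcomes, only tobacco use can have a baseline value of its own.

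**Step 2. The plan's own figures.** From Sample size estimation: 1600 recruited, 1.5% pregnancy loss, at least 90% follow-up, two-sided 2.5% level.

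- 1600 × 0.985 × 0.90 = 1418.4, so the stated 1418 reproduces.
- With 709 per arm, power is 95.7% for 40% against 30%, 94.5% for 20% against 12.5%, and 93.6% for a standardised difference of 0.2. All agree with the stated minimum of 90%.

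This point does not challenge the sample size.

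**Step 3. Effect of adding the baseline value, continuous outcomes.** The residual variance is multiplied by 1 − rho², the interval width by √(1 − rho²), and the effective sample size by 1/(1 − rho²). Here rho is the correlation that remains after the stratification and minimisation variables. The article gives no value, so the rows are assumptions. The last column is (1.960 + 1.282) × √(1 − rho²) × √(4/1418), in SD units, at a two-sided 5% level.

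| rho (assumed) | Variance reduction | Interval width × | Effective N from 1418 | Detectable at 90% power |
|---|---|---|---|---|
| 0 | 0% | 1.000 | 1418 | 0.172 SD |
| 0.3 | 9% | 0.954 | 1558 | 0.164 SD |
| 0.5 | 25% | 0.866 | 1891 | 0.149 SD |
| 0.7 | 49% | 0.714 | 2780 | 0.123 SD |

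**Step 4. Power.** The 2.5% level is justified in the article by multiple primary outcomes, and results are to be shown with 95% intervals, so 5% is used here. The 90% follow-up is stated for the three primary outcomes obtained from records. The secondary scales come from interviews, so 80% and 70% are added as assumptions: 1600 × 0.985 × 0.80 = 1261 and 1600 × 0.985 × 0.70 = 1103.

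Power = Φ(0.2 × √N / (2√(1 − rho²)) − 1.960).

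| N | rho 0 | rho 0.3 | rho 0.5 |
|---|---|---|---|
| 1418 | 96.5% | 97.7% | 99.2% |
| 1261 | 94.4% | 96.1% | 98.4% |
| 1103 | 91.3% | 93.6% | 97.0% |

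The gain is about 1 to 2 points at rho 0.3 and about 3 to 6 points at rho 0.5. It is larger for smaller effects: for 0.15 SD at N = 1418, power rises from 80.6% to 84.1% at rho 0.3 and to 90.3% at rho 0.5.

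**Step 5. Binary outcomes.** The factor 1 − rho² does not carry over to logistic regression. Adding a prognostic covariate changes the target to a conditional odds ratio and raises the power to detect it, but does not narrow its interval.

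**The case against.** The strongest reply is that the plan adjusts for baseline wherever its primary outcomes allow it. Birth weight, child emergency attendance and second pregnancy cannot have a baseline value; tobacco use can, and its model includes one. Carrying the same analyses over would then bring the tobacco model to any continuous secondary outcome with a baseline. This stands in part: the article does not exclude baseline adjustment. But it does not provide for it either, since the stated selector is the type of data.

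A second reply is that outcome-specific covariates are usually left to an analysis plan, which is not shown and may settle the matter. That is fair, and it limits the weight of the point. The article is not silent, however: it states a rule for secondary outcomes, and that rule can be improved as written.

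Three stronger readings are tempting and not supported.

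- A reader might infer that secondary models are restricted to the minimisation variables. That is the likelier reading, but the text does not say so.
- A reader might infer that the secondary results would be biased. Under randomisation, the analysis without the baseline value is unbiased, and the imbalance-triggered repeat is described as a check, not as a replacement for the main estimate.
- A reader might infer that intervals for the self-sufficiency measures, such as NEET status, employment and benefits, are needlessly wide. These are naturally binary or categorical, so that argument fails for them.

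**Conclusion.** The point holds as an efficiency and pre-specification matter for continuous secondary outcomes: seven clearly, nine if adaptive functioning and CRAFFT are scored as scales. The article collects their baseline values but does not commit the main models to use them, and the only other written route depends on observed imbalance.

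The size rests on a correlation that the article does not give. If rho is near 0.3 the gain is modest; at 0.5 or above it equals at least a third more participants (1/0.75 = 1.33). For a 0.2 SD difference, power already exceeds 90% without the baseline value in every 5% scenario shown, so the practical benefit is narrower intervals and better power for smaller effects. The primary outcomes and the sample size are not affected.

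**What to change.** Extend the sentence on secondary outcomes, for example: *Each continuous secondary outcome that was also measured at baseline will be analysed with its baseline value as a covariate in the main model, in addition to the stratification and minimisation variables and regardless of observed imbalance, as for prenatal tobacco use. Missing baseline values will be handled by mean imputation or a missing indicator, so that no participant is lost.*

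State whether adaptive functioning and CRAFFT are analysed as scales. For binary secondary outcomes, baseline adjustment is optional; if it is used, report the odds ratio as conditional on baseline status.

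The cost is one or two sentences of text, here or in the analysis plan. It needs no new data, visits or participants.

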#### Process evaluation analysis

To establish internal validity, a sample of audio-recorded pregnancy, infancy, and toddlerhood home visits will be compared for self-reported and independently established programme content, using descriptive statistics. Similarly, a sample of FNP practitioners will be examined on the MI specific competency of their programme delivery using the Motivational Interviewing Treatment Integrity (MITI) validated scale ratings [77]. Dose and structure of visits will be monitored and compared to pre-set targets. Recruitment and retention to the trial will be monitored on an ongoing basis. Contamination between trial arms will be established using descriptive statistics from the service mapping survey and follow-up trial questionnaires. The full trial data set will be subjected to subgroup analyses to determine potential environment influences on implementation and outcomes.

### Cost effectiveness/health economics analysis

#### Costs

For the primary analysis, the resource use data related to health care services utilised by the trial participants such as GP visits, hospital overnight stays, accident and emergency attendances will be considered. These data will be collected for both intervention and control arm from self-reported questionnaires, the NHS Hospital Episode Statistics and patient records held at GP practices. For the secondary analyses, in addition to the health care resource usage, non-health care costs will be included. These relate to services such as social assistance, housing, education and criminal justice. The data for this type of resource usage will be collected from the self-reported questionnaires.

The cost of the intervention will be assessed based on the routine data collected by the FNP nurses and input into the central Department of Health FNP database. This includes information directly related to the FNP utilisation such as the number and percentage of completed visits by the FNP nurses as well as their duration, and the number of telephone encounters with the client. In addition, the database includes information on the qualifications of the FNP nurses which will be used to assess the remuneration bracket of the nurses for the overall costing of this service.

#### Outcomes

For the economic analysis, the same primary outcomes that have been considered in the statistical analysis will be used. These will be analysed and reported as outcomes in a cost-consequences analysis or, wherever this is appropriate, in a cost-effectiveness analysis. Where data allow, these effectiveness estimates will be linked to utility scores and a cost-utility analysis will be conducted. A cost-utility analysis will be used for estimating the impact of the programme on maternal health. The outcome for this analysis is measured by calculating quality-adjusted life years (QALYs). Direct estimation of QALYs is not possible for children as they will be too young during the trial, but we will estimate the intervention impact upon the mothers using the EQ-5D. The cost-utility analysis will be based on the QALYs difference of the mothers between the two arms from 34-36 weeks gestation of the index child and up to the second birthday of that child, when the trial is completed.

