***Use of services***								
Dental care							***x***	
Antenatal care (check-ups, planned / unplanned attendances)			***x***					***x***
Primary care or secondary care attendance / admission		***x***		***x***	***x***	***x***		***x***
Additional non-health (education, social, childrens, Connexions) services				***x***	***x***	***x***	***x***	
Foster care (mother, baby, both)				***x***	***x***	***x***	***x***	

^1^ Name of validated measure (items amended or partially sourced from existing measures indicated by citation only) ^2^ For period from recruitment or birth until 24 months (mother and child); ^3^ Primary outcome domain.

**Table 2 T2:** Parenting and child outcomes and assessment points

**Outcome (name of measure**^**1**^**)**	**Baseline**	**34-36weeks**	**Birth record**	**6 months**	**12 months**	**18 months**	**24 months**	**HES / GP**^**2**^

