## Methods

### Trial design

This trial is an individually randomised controlled trial with a parallel economic modelling study. Trial participants ***either*** receive usual universal services ***or*** usual universal services along with regular visits from trained Family Nurses (FN) from early pregnancy (of their first child) until the child is two years old, following a prescribed programme.

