### Eligibility criteria

Eligibility criteria will match FNP programme enrolment criteria as closely as possible and are listed in full in Table 4. Recruits will be nulliparous, aged 19 or under, and will be recruited to the trial no later than 24 weeks gestation (and ideally within the first 15 weeks). This was to enable enrolment to the FNP (for those randomised to the intervention arm) in line with the programme fidelity requirements (60% of clients to be enrolled by 16 weeks gestation, and all by 28 weeks [47,48,72]).

**Table 4 T4:** Participant inclusion/exclusion criteria

**Inclusion criteria**	**Exclusion criteria**
1. Women aged 19 or under (at recruitment / consent).	1. Women who at study entry, plan to have their child adopted.
2. Lives within the catchment area covered by the local FNP team.	2. Women who at study entry, plan to leave the FNP area during the time of the trial either for an extended period of time (3 months or longer) or permanently.
3. First pregnancy confirmed by health services (including those expecting multiple births) unless previous pregnancy ended in miscarriage, stillbirth or termination.	3. Women who would require a third person (translator, sign interpreter) to receive the FNP programme.
4. Recruited no later than 24 weeks gestation.	
5. Gillick competent to provide informed consent to research participation including competence in English at conversational level or higher.	

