### Randomisation

Prior to recruitment of a trial participant, the Local Researcher will confirm that the local FNP team has spare capacity, consent will be obtained and the baseline assessments completed. The Local Researchers will use a remote randomisation service (automated telephone or web) provided by Bristol Randomised Trials Collaboration (BRTC) to allocate the woman to FNP or usual care. The Local Researcher will inform the FNP team of participants allocated to receive the programme. The FNP team will then take responsibility to enrol the woman into the programme and provide the intervention. For women allocated to usual care, the woman’s community midwife will be informed. All participants’ General Practitioners will be notified of their recruitment to the trial.

A randomisation algorithm will minimise by gestation at recruitment (<16 weeks/16 weeks+), smoking status at recruitment (smoker/non-smoker) and first language/preferred language (English/non-English) for each site with a probability of 0.8. Therefore a random element is retained, further reducing predictability of allocation. The trial statisticians and economists will be blinded to treatment allocation until analyses are complete.

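### Maternal QALYs start at 34-36 weeks gestation, after randomisation, although EQ-5D is collected at baseline and the cost sources reach further back

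*Protocol article*

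**What the plan says.** All references are to the protocol article.

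- **QALY window.** Under Cost effectiveness/health economics analysis, Outcomes, the cost-utility analysis uses the mothers' QALY difference "between the two arms from 34-36 weeks gestation of the index child and up to the second birthday of that child". No reason is given for that starting point.
- **EQ-5D schedule.** Table 1, in the row that begins "General health status (EQ-5D) [52", marks baseline, 34-36 weeks, and 6, 12, 18 and 24 months: six assessments.
- **Order of events.** Under Randomisation, "consent will be obtained and the baseline assessments completed" before the remote service allocates the woman. Under Eligibility criteria, women are "recruited to the trial no later than 24 weeks gestation (and ideally within the first 15 weeks").
- **Cost sources.** Under Costs, health-care use comes from "self-reported questionnaires, the NHS Hospital Episode Statistics and patient records held at GP practices". Footnote 2 to Table 1 describes the hospital and GP data as "For period from recruitment or birth until 24 months (mother and child"). The cost of the programme rests on a database that holds "the number and percentage of completed visits by the FNP nurses as well as their duration", and Trial design has the visits running "from early pregnancy (of their first child) until the child is two years old". The Costs section names no date from which costs are counted.
- **Combination.** Data analysis and presentation of the results divides the cost difference by the QALY difference, and adds acceptability curves. Both differences come from a regression that may include covariates, which are not named.

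**The concern.** In a randomised comparison, the natural origin for costs and effects is randomisation. Here a baseline utility is measured just before allocation, yet the stated window opens at an assessment made after allocation, when women in the intervention arm may already be receiving visits. The area between the baseline and 34-36 week utilities is discarded although both ends are measured.

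The cost sources appear to run from enrolment or recruitment. If costs are counted as those sources permit, the numerator of the cost per QALY includes weeks that the denominator leaves out. A programme that changed maternal utility before 34-36 weeks would have the cost of that phase counted and its QALYs from that phase left out. If the early change were a gain, the ratio would be too high; if it were a loss, the ratio would look too favourable.

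**Working it through.** The plan states no QALY figure, ICER or cost-utility sample size, so there is nothing to reproduce. The check is of time windows, followed by an illustration in QALYs.

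**Inputs from the article:** QALY start at 34-36 weeks (Outcomes); recruitment by 24 weeks, ideally within 15 (Eligibility criteria); end at the second birthday.

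**Assumptions:** birth at 40 weeks; two years = 2 × 52.18 = 104.36 weeks; randomisation at the gestation of recruitment, g.

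**Step 1: omitted time.**
Omitted weeks = (34 or 36) − g. Whole window = (40 − g) + 104.36 weeks.

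| Recruited at g (weeks) | Omitted weeks | Whole window (weeks) | Share omitted |
|---|---|---|---|
| 24 | 10-12 | 120.36 | 8.3-10.0% |
| 20 | 14-16 | 124.36 | 11.3-12.9% |
| 16 | 18-20 | 128.36 | 14.0-15.6% |
| 15 | 19-21 | 129.36 | 14.7-16.2% |

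These are shares of calendar time since recruitment. They are neither shares of QALYs nor durations of programme exposure.

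**Step 2: what that could mean in QALYs.** The documents give no utility difference. Assume a between-arm difference of 0 at baseline that rises in a straight line to u at 35 weeks and then stays at u.

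- Omitted = (u/2) × (35 − g)/52.18
- Counted = u × (5 + 104.36)/52.18
- Omitted/counted = (35 − g)/(2 × 109.36), whatever the value of u

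Results:

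- g = 24: 11/218.72 = 5.0%
- g = 16: 19/218.72 = 8.7%
- g = 15: 20/218.72 = 9.1%

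For example, with u = 0.02 the counted difference is 0.042 QALY, and the omitted difference is 0.002 (g = 24) to 0.004 (g = 16). With costs unchanged, the ratio on the stated window would be about 1.05 to 1.09 times the ratio on the full window.

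The straight-line rise is also what an area-under-the-curve calculation would draw between the only two prenatal assessments. The assumption that carries weight is that the difference then holds. If there is no difference at 34-36 weeks, this calculation omits nothing.

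**Step 3: do the cost sources start earlier?**

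- The database of completed visits is described without any cut-off at 34-36 weeks, for a programme that begins in early pregnancy.
- The footnote to Table 1 takes the hospital and GP data back to recruitment or birth.
- Table 1 marks primary and secondary care use at the 34-36 week interview, where a woman can only report use that has already happened.

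All three reach back before the QALY window opens, and nothing in the article restricts costs to the later period. That costs will in fact be counted from then is an inference, because the Costs section does not say so.

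**The case against.** The strongest reply is that the mismatch is not written down. The footnote describes what is collected, not what is costed, and the full analysis plan may align the two periods. This stands to the extent that the article does not contradict itself on the cost period. It does not answer the QALY window, which is an explicit choice and leaves out a measurement that the trial schedules.

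Three stronger readings are tempting, and the documents do not support them.

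- *The first phase is all cost with no possible benefit.* The Outcomes text compares the arms from 34-36 weeks onward. It does not subtract or adjust for the value at that time, so a gain already present then and carried forward is counted in full. Only the area before it is lost.
- *The QALY difference is confounded with baseline utility.* Allocation is randomised. A chance difference at baseline is sampling error, and the planned regression allows covariates. An article may leave their names to the analysis plan. Chance imbalance would also affect an unadjusted QALY counted from randomisation, so it does not measure the harm of the late start.
- *The omitted weeks are weeks on the programme.* They are weeks since recruitment. Table 3 accepts programme enrolment up to 28 weeks, so exposure by 34-36 weeks can be shorter.

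It is also fair to say that the reach is limited. The four primary outcomes, the cost-consequences analysis and any cost-effectiveness analysis on those outcomes do not use this window.

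**Conclusion.** The point holds as a stated analysis choice that should be changed. The QALY window starts after randomisation and drops about 8-10% of the time to the second birthday for recruitment at 24 weeks, and 15-16% for recruitment at 15 weeks, given birth at 40 weeks. Under the illustrative pattern, the lost area is about 5-9% of the counted gain. Its true size and direction depend on whether the programme changes maternal utility before 34-36 weeks, which the documents cannot tell us.

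The start of the QALY window and the availability of the baseline EQ-5D are certain from the text. That costs start earlier than QALYs is probable rather than stated. The consequence is modest and confined to the incremental cost per QALY and its acceptability curve.

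**What to change.** Make three changes of wording in the health economics section.

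1. **Outcomes:** define maternal QALYs as the area under the EQ-5D curve from baseline to the child's second birthday, using all six scheduled assessments.
2. **Data analysis and presentation of the results:** name baseline EQ-5D as a covariate in the regression for the QALY difference. Once the area starts at baseline, a chance difference there enters it directly, so the adjustment belongs with the first change.
3. **Costs:** state that costs cover the same period as the QALYs.

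If there is a reason to keep the 34-36 week start, give it and report the baseline-start result as a sensitivity analysis.

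The baseline EQ-5D is already in the schedule, so no new data collection is needed. The cost is a little extra analysis work.
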